### Outcomes {12}

The primary endpoints of the phase 2a study are the (a) pharmacokinetic measurement of the antibody titer of XAV-19 measurements of all treated patients and of all patients in the placebo group at day 8 (3 days after the last administration) and (b) tolerability and adverse events of XAV-19 between the two groups of treated patients and vs. placebo over 29 days, evaluated as:
Occurrence of all suspected XAV-19-related adverse effects and incidence of serious adverse eventsProportion of participants with treatment emergent adverse events leading to study drug discontinuationIncidence of major or bacterial or fungal infections during the hospital stayIncidence of hypersensitivity reactions and infusion reactions. To note AEs are registered up to day 60 and for infusion-related AEs, 48 h after.White cell count, hemoglobin, platelets, creatinine, ALT, AST, on day 1, day 3, day 5, day 8, day 15, and day 29SARS-CoV-2 viral load over time (day 1–day 29), as collected by nasopharyngeal swab samplesTime to RT-PCR virus negativity in nasopharyngeal swab samples

The secondary endpoints of the phase 2a are the:
Pharmacokinetic analysis: Antibody titer measurements at day 1 (pre-dose, post-dose), at day 3, day 5 (pre-dose, post-dose), day 8, day 15, and day 29.The antibody titer of XAV-19 measurements in group 1 treated patients and group 2 treated patients at day 15.Clinical aspects:Duration of supplemental oxygenTransfer to intensive care unit with need for invasive mechanical ventilation or high flow oxygenNormalization of fever ≥24 h: clinical assessment every day from day 1 to day 14. Evaluation to be performed between 8 and 12 am, day X evaluation will consider the higher value during day X-1 (8 am to 8 am)- Normal fever (≤ 37.8 °C tympanic or ≤ 36.6 °C axillary or ≤ 37.2 °C oral taken 4 h apart from antipyretic administration) each day and time to resolution of fever for at least 48 hBiomarkers: CRP, Ferritin (at days 1, 3, 5, 8, 15, and 29)Ordinal scale assessed at Day 15. The 7-point ordinal scale is an assessment of the clinical status at the first assessment on day 15. The scale is as follows:Not hospitalized, no limitations on activitiesNot hospitalized, limitations on activitiesHospitalized, not requiring supplemental oxygenHospitalized, requiring supplemental oxygenHospitalized, on non-invasive ventilation or high flow O_2_ devicesHospitalized, on invasive mechanical ventilation or ECMODeathHospital length of stay

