The primary endpoint of the phase 2b is the time to weaning of supplemental oxygen.

If patient is still on oxygen at day 15 or if the patient is weaned but put back on oxygen, then the delay will be censored at 15 days.

The secondary endpoints are the:

National Early Warning Score (NEWS2) at day 15 and difference in NEWS2 between day 1 and day 15Clinical status using the 7-point ordinal scale assessed at day 3, day 5, day 8, day 11, day 15, and day 29Time to improvement of one category from admission using the 7-point ordinal scaleTime to first fever normalization (criteria for normalization: temperature < 36.6 °C armpit, < 37.2 °C oral, < 37.8 °C rectal or tympanic)Duration of oxygen therapy over 29 daysComparison of oxygen requirement between the two groups over 29 daysTime to weaning in supplemental oxygen and proportion without O2 requirement at day 15, according to baseline (day 1) oxygen requirement (≤ 4 L/min or 4 L/min)Incidence and duration of non-invasive ventilation or high flow oxygen devices, of invasive mechanical ventilation during the studyHospital length of stayAll-cause mortality at Day 29Safety of XAV-19 evaluated as:Occurrence of all suspected XAV-19-related adverse effects or incidence of serious adverse eventsProportion of participants with treatment emergent adverse events leading to study drug discontinuationIncidence of major or opportunistic bacterial or fungal infectionsIncidence of hypersensitivity reactions and infusion reactionsWhite cell count, hemoglobin, platelets, creatinine, ALT, AST, on day 1, day 3, day 5, day 8, day 11, day 15, and day 29SARS-CoV-2 viral load over time (day 1–day 29), as collected by nasopharyngeal swab samplesTime to RT-PCR virus negativity in nasopharyngeal swab samples

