### Adverse event reporting and harms {22}

All patients will be closely monitored during both study phases for overall biological and clinical safety data (e.g., infections or malignancies) and any drugs toxicity.

According to regulation, each AE reported by the patient or identified by the investigator must be collected and reported to sponsor, as soon as he is aware, if it meets to seriousness criteria from inclusion of the subject, to the end of the participation.

As a routine precaution, patients enrolled in this trial must be observed for at least 2 h post infusion of study drugs. Patients will be assessed for signs or symptoms of any infusion reactions (e.g., hypotension, hypoxia, tachycardia, fever, nausea, fatigue, headache, myalgia, and malaise).

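### In both phases, non-serious adverse events outside a few named categories count as an endpoint only if suspected to be XAV-19-related; all treatment-emergent events by arm is not listed.

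*Protocol article*

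**What the plan says.** **Phase 2b (Outcomes {12}, secondary endpoints).** Safety is defined by a list. Its first item is the occurrence of "all suspected XAV-19-related adverse effects or incidence of serious adverse" events. The other items are treatment-emergent events leading to discontinuation of study drug, major or opportunistic bacterial or fungal infections, hypersensitivity and infusion reactions, six laboratory tests by visit, viral load, and time to RT-PCR negativity.

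**Phase 2a (Outcomes {12}, primary endpoint (b)).** The stem announces a comparison of "tolerability and adverse events of XAV-19 between the two groups of treated patients and vs. placebo over 29 days". The list that follows opens with "Occurrence of all suspected XAV-19-related adverse effects and incidence of serious adverse" events and continues much as in phase 2b.

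**Collection.** The phase 2a list adds: "To note AEs are registered up to day 60 and for infusion-related AEs, 48 h after". Adverse event reporting and harms {22}, which covers both phases, says that "each AE reported by the patient or identified by the investigator must be collected and reported to sponsor". The same sentence then requires prompt notification and makes something conditional on the event meeting seriousness criteria.

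**The concern.** In a randomised, double-blind, placebo-controlled trial, the count of all treatment-emergent events by arm is protected by randomisation and needs no opinion on cause. An endpoint restricted to suspected-related events puts a case-by-case judgement in front of that comparison.

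The judgement is hard to make here. Section {22} gives fever, headache, myalgia and hypoxia among the signs of infusion reaction. The background section and the inclusion criteria give fever, headache, myalgias and dyspnoea or shortness of breath as COVID-19 symptoms. When phase 2b starts, planned prior exposure to XAV-19 is 2 cohorts × 6 = 12 treated patients.

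At stake is a real excess of non-serious events that investigators put down to the disease and that no other listed item catches. Safety is a primary objective in phase 2a and a stated secondary objective in phase 2b.

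**Working it through.** **Step 1: which events count.** Reading the two lists in Outcomes {12} side by side:

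| Type of event | Phase 2a | Phase 2b |
|---|---|---|
| Serious, any cause | counted | counted |
| Non-serious, suspected related | counted | counted |
| Non-serious, not suspected, leads to discontinuation | counted | counted |
| Non-serious, not suspected, infection of the named kind | counted | counted |
| Non-serious, not suspected, hypersensitivity or infusion reaction | counted | counted |
| Non-serious, not suspected, seen in the listed laboratory tests | through the laboratory item | through the laboratory item |
| Any other non-serious event, not suspected | **not counted** | **not counted** |
| All treatment-emergent events by arm | **not listed** | **not listed** |

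The phase 2a stem speaks of adverse events versus placebo with no relatedness condition. Its own list then narrows that.

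**Step 2: are the events recorded?** For phase 2a, the day-60 sentence registers adverse events without a relatedness or seriousness limit. For phase 2b, only section {22} bears on this. It can be read as all events collected and only serious ones notified at once, or as both duties applying to serious events. The article does not settle which.

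**Step 3: is there a figure to reproduce?** No. The article gives no adverse-event rates, and phase 2b is sized on oxygen weaning. What follows is an illustration on assumed rates.

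Inputs: n = 352 / 2 = 176 per arm (Sample size {14}, 1:1 allocation); two-sided 5% (assumed); any-event rates of 40% on placebo and 55% on XAV-19 (assumed), an excess of 15 points. Let *a* be the share of background events called related and *b* the share of drug-caused excess events called related. Then:

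- related rate on placebo: p0 = 0.40*a*
- related rate on XAV-19: p1 = 0.40*a* + 0.15*b*
- power = Φ{ [ |p1 − p0| − 1.96 √(2p̄(1 − p̄)/n) ] / √([p0(1 − p0) + p1(1 − p1)]/n) }, with p̄ the mean of p0 and p1

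All events, 0.40 against 0.55: (0.15 − 1.96 × 0.0532) / 0.0526 = 0.868, so power is 81%.

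Related only, *a* = 10% and *b* = 50%: p0 = 0.04, p1 = 0.115; (0.075 − 1.96 × 0.0285) / 0.0282 = 0.678, so power is 75%.

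| Background called related (*a*) | *b* = *a* | *b* = 50% | *b* = 70% |
|---|---|---|---|
| 10% | 10% | 75% | 93% |
| 20% | 16% | 59% | 83% |
| 30% | 23% | 49% | 74% |

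With 50% against 65% instead, all events give 82% (0.815), and the same grid runs from 9% (*a* = *b* = 10%) to 90% (*a* = 10%, *b* = 70%).

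Power on the related subset can thus be far below, or somewhat above, power on all events. One result does not depend on the background share: the related-only difference is 0.15*b*, so it recovers only the fraction *b* of the true excess. At *b* = 50% it shows 7.5 points where the excess is 15.

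**The case against.** Much of the case on the other side stands, and it rules out several stronger readings.

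- **That only suspected-related and serious events count.** A reader might infer this from the first item alone. The rest of the list contradicts it: discontinuations, infections, hypersensitivity and infusion reactions, and laboratory values have no stated suspicion filter.
- **That harm resembling COVID-19 drops out of the trial.** Phase 2b compares NEWS2, the 7-point scale, oxygen requirement, ventilation, fever normalisation, length of stay and all-cause mortality with no causality condition, and serious events count whatever their cause. What escapes is narrower: non-serious, non-discontinuing events outside all of these.
- **That investigators have no human experience to judge from.** The statement that XAV-19 has never been given to humans describes the position before phase 2a. Trial status reports that phase completed before phase 2b began, and there is experience with LIS1 on the same platform.
- **That the phase 2b events are certainly on file.** The seriousness clause in section {22} prevents that conclusion.
- **That power collapses to 10% to 23%.** This holds only if background and drug-caused events are called related equally often. The article supports neither that nor any other pair of shares.
- **That *and* in phase 2a and *or* in phase 2b define different endpoints.** Both phases name the same two components, so this is a wording matter.

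It can also be said that all-cause tables by arm are routine analysis-plan content and that nothing in the article forbids them. That is fair, and the full protocol or analysis plan may contain them. It does not remove the point, because the relatedness condition is written into the endpoint that the article states.

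**Conclusion.** The concern holds in limited form. Both safety lists restrict the general adverse-event item to suspected-related effects plus serious events, and neither makes all treatment-emergent events by arm an endpoint. Phase 2a does so after announcing an unrestricted comparison with placebo. The part left out is non-serious events, not suspected to be drug-related, outside the named categories.

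No single figure for the loss is defensible. On the assumed rates of 40% against 55%, power on the related subset lies between about 10% and 93% over the attribution shares shown, against 81% on all events. The firmer argument is about what is estimated: the related-only difference understates the excess by a fraction that the trial cannot observe. The primary efficacy analysis of phase 2b is not affected. The amendment should be made, since it is cheap and gives a safety measure that does not depend on causality opinion.

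**What to change.** 1. In Outcomes {12}, use identical wording for both phases and list separately: (1) patients with any treatment-emergent adverse event, regardless of causality; (2) patients with any serious adverse event; (3) patients with a suspected-related event, as supportive. Report each by arm with the difference and 95% CI. This also removes the *and*/*or* ambiguity. Keep the other listed safety items.
2. In Adverse event reporting and harms {22}, separate recording from prompt notification, and state that all adverse events, not only serious ones, are recorded in phase 2b.
3. Trial status reports phase 2a as complete. Its tables can be drawn from the events already registered and marked as added.

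Cost: wording and a few extra tables if non-serious events are already recorded in phase 2b, and somewhat more data entry if they are not. If a power illustration is shown, give it as a range over differing attribution shares for background and drug-caused events.

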### Participant timeline {13}

For the phase2a study: The treatment duration per patient will correspond to the infusion made at day 1 and day 5, the patient’s follow-up to 2 months, and the recruitment period to 2 months.

For the phase2b study: The treatment duration per patient also will correspond to the infusion made at day 1 and day 5, the patient’s follow-up to 2 months, and the recruitment period to 6 months.

### Sample size {14}

As it is a phase 2a, the number of patients was determined according to phase 2a’s relevant publications [23–25] . It was decided to enroll two cohorts of 8 patients (6 treated patients and 2 matching placebo in each cohort).

For the phase 2b, the predetermined sample size, controlling for the α risk of 5% and power of 80%, is 352 participants, based on an expected survival rate of patients giving up oxygen therapy at least at day 15 of 80% in the control group and 90% in the experimental group. In addition, the median duration of oxygen therapy in the control group is 8 days, and in the experimental group is 6 days. Hence the estimated hazard ratio is 0.75. The sample size was calculated following the formula of Schoenfeld [26] and the hazard ratio was estimated thanks to Cortes’ publication [27].

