## Assignment of interventions: allocation

### Sequence generation {16a}

Randomization will be performed and balanced by blocks. The software used for the randomization is SAS version 9.4.

In terms of the ratio, for phase 2a, the first 2 patients in each cohort will have a ratio of 1:1, and if all goes well, the remaining 6 patients in the 2 cohorts will have a ratio of 1:5 (1 placebo for 5 doses of XAV-19). For the phase 2b, it will be carried out in a 1:1 ratio.

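### The phase 2b size of 352 follows from its stated inputs only at an undeclared one-sided 5% alpha; at two-sided 5% the power for the stated hazard ratio of 0.75 is about 70%, not 80%.

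*Protocol article*

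**What the plan says.** The section Sample size {14} of the protocol article states that the phase 2b size, for an alpha "risk of 5% and power of 80%, is 352 participants". It does not say whether the 5% is one-sided or two-sided. The other inputs are in the same paragraph:

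- the method, which is Schoenfeld's formula;
- weaning from oxygen "at least at day 15 of 80% in the control group and 90% in the experimental group";
- median times on oxygen of 8 days (control) and 6 days (XAV-19);
- the effect size drawn from these: "Hence the estimated hazard ratio is 0.75".

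On allocation, Sequence generation {16a} says "For the phase 2b, it will be carried out in a 1:1 ratio". Under Outcomes {12} the primary endpoint is time to weaning, and for a patient still on oxygen at day 15, or weaned and later returned to it, "then the delay will be censored at 15 days".

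The phase 2b primary objective (Objectives {7}) and the statistical methods section {20a} both describe a comparison between the two groups without a direction. Section {20a} does not name the primary test. No interim analysis is planned {21b}, no missing primary data are expected {20c}, and no allowance for dropout is stated.

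**The concern.** The article prints every input that the formula needs except the sidedness of alpha, so the figure can be checked. A reader who meets a 5% alpha beside a comparison without direction will normally take it as two-sided. On that reading the printed inputs do not lead to 352.

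The error rates of the primary efficacy comparison are at stake. If the analysis is two-sided at 5%, the chance of missing an effect of the stated size is about 30% instead of the stated 20%. If it is one-sided at 5%, the power statement is right, but the chance of wrongly declaring benefit is 5%, twice the 2.5% in that direction of a two-sided 5% test. The article gives readers no means of telling which applies.

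A second, smaller question is where the hazard ratio of 0.75 comes from, since the paragraph offers both medians and day-15 rates and they do not lead to the same ratio.

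**Working it through.** **Inputs.** From Sample size {14}: alpha 5%, power 80%, hazard ratio 0.75, weaned by day 15 of 80% and 90%, Schoenfeld's formula. From Sequence generation {16a}: 1:1 allocation. Mean event fraction: (0.80 + 0.90)/2 = 0.85.

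**Formula.** For 1:1 allocation, events D = 4(z_alpha + z_beta)² / (ln HR)², and patients N = D / 0.85. Here (ln 0.75)² = 0.0828 and z_beta = 0.842.

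**Reproducing the plan's figure.**

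| Alpha | z_alpha | Events | Patients |
|---|---|---|---|
| One-sided 5% | 1.645 | 298.8 | 351.5, so 352 |
| Two-sided 5% | 1.960 | 379.4 | 446.3, so 447 |

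The one-sided result matches exactly. The two-sided result is 447 − 352 = 95 patients higher.

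**Could another two-sided calculation give 352?** None that was tried at a hazard ratio of 0.75 does. Rounding events up to 380, event fractions of 0.80, 0.85, 0.90 and 1.0 give 475, 447, 422 and 380 patients. Freedman's formula needs 385 events and gives 481, 453, 428 and 385. Comparing 80% with 90% as two proportions needs 398 patients two-sided, or 438 with continuity correction. The one-sided version with continuity correction gives 354, close to 352, but it too is one-sided and is not the formula that the article names.

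**Power at 352.** Expected events are 352 × 0.85 = 299.2. Power = Φ(√D/2 × |ln HR| − z_alpha).

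- Two-sided, hazard ratio 0.75: Φ(8.649 × 0.2877 − 1.960) = Φ(0.528) = 70.1%.
- One-sided, hazard ratio 0.75: 80.0%.
- Two-sided, event fraction 0.80 to 0.90: 67.5% to 72.6%.
- Two-sided, if all 352 patients were weaned: 77.0%, still below 80%.

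Hazard ratio with 80% two-sided power at 299.2 events: exp(−2 × 2.8016/√299.2) = 0.723.

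**Where 0.75 comes from.** It equals 6/8, the ratio of the median durations. That ratio is the hazard ratio only if hazards are constant. Under proportional hazards the day-15 rates give ln(0.20)/ln(0.10) = 0.699. At that value, two-sided 5% and 80% power need 245 events, about 288 patients, and 352 patients have about 87% power. So 0.70 does not explain 352 either, unless an unstated inflation of about 18% is supposed (1 − 288/352 = 0.18).

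**The case against.** The strongest reply is that there is no arithmetic slip. The stated formula, ratio, rates and power reproduce 352 exactly, and one word is missing. The article condenses a fuller protocol, the analysis plan is not shown, and the primary test is not named, so no stated two-sided test contradicts the sizing. One-sided 5% is also a possible choice in phase 2. All of that stands as far as it goes, and it is why the 70% is conditional on a two-sided analysis. It does not remove the point. The article prints a size, an alpha and a power that agree only under a condition it leaves out, and its usual reading gives a different power.

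A second reply is that 70% shows only the unfavourable side. This also stands in part. The article's own day-15 rates imply a larger effect (about 0.70), for which two-sided power is about 87%. The article, however, says that the ratio is 0.75, and 352 was evidently derived from that value.

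A reader might also infer that the medians and the day-15 rates contradict each other, because constant hazards with medians of 8 and 6 days give 72.7% and 82.3% weaned by day 15. The article never assumes constant hazards for those rates. A common Weibull shape of about 1.32 with the same medians gives 79.6% and 90.2%, so the four figures fit together. The hazard ratio of 0.75 is the input that does not fit them: that shape implies 0.75^1.32, about 0.68.

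Finally, a reader might see an error in a ratio below 1 when weaning is the event and benefit would give 1.33. Schoenfeld's formula uses the squared logarithm, so 0.75 and 1.33 give the same size.

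**Conclusion.** The point holds. The phase 2b size rests on a one-sided 5% alpha that the article does not declare. If the primary comparison is made at two-sided 5%, 352 patients give about 70% power at the stated hazard ratio of 0.75, and 80% only at about 0.72; the stated 80% would need about 447 patients. These figures assume Schoenfeld's formula, 1:1 allocation, no loss of patients and the article's mean event fraction of 85%.

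The documents do not support the flat statement that the trial is underpowered. Sidedness is unstated, and under the ratio implied by the day-15 rates (about 0.70) two-sided power would be about 87%. What can be said is that the printed combination of 5%, 80%, 0.75 and 352 is correct only one-sided, and that the choice of 0.75 over the ratio implied by the day-15 rates is unexplained. Because this concerns the error rates of the primary efficacy comparison, it should be settled before the blind is broken.

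**What to change.** Choose one of two wordings for Sample size {14}:

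1. Declare the alpha as one-sided 5%, give the reason, and use the same one-sided test in the phase 2b primary analysis.
2. Keep two-sided 5%, and restate the power of 352 patients as about 70% at a hazard ratio of 0.75, or 80% at about 0.72.

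In either case, state whether the hazard ratio rests on the ratio of medians or on the day-15 rates, and give the power that follows from that choice.

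The cost is wording in the protocol and the analysis plan. No extra patients are needed for either option. The price is that the stated alpha or the stated power will look less favourable than it does now.

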### Recruitment {15}

Recruitment is planned over a period of 4 months for the phase 2a study and 6 months for phase 2b study. The number of open investigator centers compensates for the short duration of inclusion.

## Assignment of interventions: allocation

### Sequence generation {16a}

Randomization will be performed and balanced by blocks. The software used for the randomization is SAS version 9.4.

In terms of the ratio, for phase 2a, the first 2 patients in each cohort will have a ratio of 1:1, and if all goes well, the remaining 6 patients in the 2 cohorts will have a ratio of 1:5 (1 placebo for 5 doses of XAV-19). For the phase 2b, it will be carried out in a 1:1 ratio.

